**Methods/Design:**

This is a multicenter randomized controlled trial (RCT), with cluster assignment by health center and two parallel arms. Two interventions will be applied by FPs, usual care versus the new intervention predictD-CCRT. The latter has four components: a training workshop for FPs; communicating the level and profile of risk of depression; building up a tailored bio-psycho-family-social intervention by FPs to prevent depression; offering a booklet to prevent depression; and activating and empowering patients. We will recruit a systematic random sample of 3286 non-depressed adult patients (1643 in each trial arm), nested in 140 FPs and 70 health centers from 7 Spanish cities. All patients will be evaluated at baseline, 6, 12 and 18 months. The level and profile of risk of depression will be communicated to patients by the FPs in the intervention practices at baseline, 6 and 12 months. Our primary outcome will be the cumulative incidence of major depression (measured by *CIDI* each 6 months) over 18 months of follow-up. Secondary outcomes will be health-related quality of life (*SF-12* and *EuroQol*), and measurements of cost-effectiveness and cost-utility. The inferences will be made at patient level. We shall undertake an intention-to-treat effectiveness analysis and will handle missing data using multiple imputations. We will perform multi-level logistic regressions and will adjust for the probability of the onset of major depression at 12 months measured at baseline as well as for unbalanced variables if appropriate. The economic evaluation will be approached from two perspectives, societal and health system.

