### Sample size

The sample size was calculated assuming that the cumulative incidence of depression in the control group will be 12% [34] while the incidence in the intervention group will be 5 points below that 12%. The Type I error of the chosen contrast was 5% and the power 80%. The sample size obtained assuming a simple random sample would be 430 people in each group. As we will undertake a cluster randomization (by health center), and decided to have 35 health centers in the control group and 35 in the intervention group (48 patients in each health center), we obtained an effect design of 3.82, with the assumption that the intraclass correlation coefficient of the health center is 0.06 [34]. Thus we need a sample size of 1643 patients in each trial arm, making a global sample of 3286 patients, 140 family doctors and 70 health centers. These calculations assume that the distribution of 2 FPs per health center and 24 patients per FP will be very homogeneous (coefficients of variation of cluster sizes <0.15). We also expect to increase the sample of patients recruited by FPs from 24 to 26–27, since about 10% of potential patients will have a diagnosis of major depression on CIDI at baseline and will need to be excluded.

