If many health centers and FPs refuse to participate, we could encounter a selection bias as the FPs who choose to participate may have a different profile (psychosocial orientation, different training and work satisfaction, etc.) to those who do not. This could limit external validity [110] and, from a pragmatic standpoint, the new intervention would be less effective when applied as a general program. Similar biases could occur if a large proportion of patients refuse to participate. It is not easy to obtain information from those physicians and patients who refuse to participate, so it will be difficult to ascertain the direction of this possible selection bias. As stated above, for the analyses with complete cases we will use the inverse probability weighting [84,85] to adjust for a possible attrition bias due to participants lost during the follow-up. We will use multiple imputations to minimize attrition bias and maintain statistical power [78,111].

The results obtained will be applicable to primary care attendees and cannot necessarily be generalized to other settings such as the general population. Nevertheless, primary care is an ideal setting for prevention and attendees are generally (because of health and social problems) at greater risk of depression than the general population.

If the predictD-CCRT intervention proves effective, it will be difficult to determine which of the 5 components are active or expendable, and how each interacts with the others. We will conduct a number of secondary analyses that could provide clues to the most relevant component, but more studies (quantitative and qualitative) specifically directed toward that goal will be needed.

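### The 80% power makes no allowance for 18-month loss, which costs little, and rests on a base of 430 that fits only a one-sided 5% test, with sidedness unstated

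*Protocol article*

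**What the plan says.** The Sample size section takes as its inputs "assuming that the cumulative incidence of depression in the control group will be 12" per cent and "the incidence in the intervention group will be 5 points below that 12" per cent, that is, 12% against 7%. On error rates it says "The Type I error of the chosen contrast was 5% and the power 80" per cent, without saying whether the test is one- or two-sided. It then gives the base figure: "The sample size obtained assuming a simple random sample would be 430 people in each group". With 35 centres per arm, 48 patients per centre and a centre-level intraclass correlation of 0.06, it obtains a design effect of 3.82 and concludes: "Thus we need a sample size of 1643 patients in each trial arm, making a global sample of 3286 patients".

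The abstract uses that number as the enrolment target: "We will recruit a systematic random sample of 3286 non-depressed adult patients (1643 in each trial arm".

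The only inflation given is from 24 to 26–27 patients per family physician, and the reason is exclusion at entry: "since about 10% of potential patients will have a diagnosis of major depression on CIDI at baseline". No rate of loss to follow-up is stated.

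Losses are nevertheless expected. The Inverse probability weighting section models who remains at 18 months and weights the complete-case analysis accordingly. The Strengths and limitations section says: "We will use multiple imputations to minimize attrition bias and maintain statistical power".

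**The concern.** A sample-size formula gives the number of patients who must contribute an outcome. Here that number is also the number enrolled, and the plan itself expects some of those patients to be lost. The stated 80% is therefore power at full follow-up. The remark that imputation will maintain power may lead a reader to think the gap is already closed.

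Reproducing the 430 raises a second question about the same 80%: which test it belongs to. If the analysis is read two-sided, the stated power is too favourable before any patient is lost.

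What is at stake is how a null result is read. It would be judged against an 80% chance of detecting a 5-point reduction, a figure that the document does not support for the number analysed or, with a two-sided test, for the number enrolled.

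**Working it through.** **Inputs from the Sample size section:** p1 = 0.12, p2 = 0.07, difference d = 0.05, alpha 5%, power 80%, k = 35 centres per arm, 48 patients per centre, intraclass correlation 0.06, N = 1643 per arm. **Assumed, because the document gives no figure:** loss of 10%, 20% or 30%, spread evenly over centres.

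**1. The base figure of 430.** With p̄ = 0.095, √(2p̄(1−p̄)) = √0.17195 = 0.4147 and √(p1(1−p1)+p2(1−p2)) = √0.1707 = 0.4132,

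n = [zα × 0.4147 + 0.8416 × 0.4132]² / 0.05².

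- One-sided 5% (zα = 1.645): n = 425. With unpooled variance it is about 422, and with continuity correction 464.
- Two-sided 5% (zα = 1.960): n = 539. With unpooled variance it is 536, with the arcsine form 531, and with continuity correction 578.

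Only the one-sided, uncorrected forms come close to 430. At exactly 430 per arm, power is 80.5% one-sided and 70.6% two-sided.

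**2. The design effect and the 1643.** 1 + (48 − 1) × 0.06 = 3.82, and 430 × 3.82 = 1642.6, rounded to 1643. The plan's arithmetic is reproduced, and it contains no term for loss.

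**3. The 26–27 per physician.** After 10% exclusion, 26 × 0.9 × 140 = 3276 and 27 × 0.9 × 140 = 3402. This brings the total back to about 3286. The nominal 24 × 140 = 3360 (1680 per arm) is about 2% above 3286.

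**4. Power after loss.** If the 35 centres stay, losing patients also shrinks the clusters, so the design effect must be recalculated:

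m = N(1 − loss)/35; DE = 1 + (m − 1) × 0.06; effective n = N(1 − loss)/DE; power = Φ{[√(effective n) × 0.05 − zα × 0.4147] / 0.4132}.

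| Assumed loss | m | DE | Effective n per arm | Power, one-sided 5% | Power, two-sided 5% |
|---|---|---|---|---|---|
| 0% | 46.9 | 3.76 | 437 | 81.1% | 71.4% |
| 10% | 42.2 | 3.47 | 426 | 80.1% | 70.2% |
| 20% | 37.6 | 3.19 | 412 | 78.9% | 68.7% |
| 30% | 32.9 | 2.91 | 395 | 77.5% | 66.9% |

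Effective n stays at or above 430 up to about 6% loss.

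**5. Separating the two effects.** With no loss, moving from one- to two-sided costs 81.1 − 71.4 = 9.7 points. A 20% loss costs 81.1 − 78.9 = 2.2 points one-sided, or 71.4 − 68.7 = 2.7 points two-sided.

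**6. Less benign loss (also assumed).** If 2 of 35 centres per arm withdraw and 20% of the remaining patients are lost, power is about 77% one-sided and 66% two-sided. It is about the same if 20% loss is uneven enough to raise the coefficient of variation of cluster size to 0.3, where the plan assumes below 0.15.

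**The case against.** The case for leaving the figure alone has five parts.

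- **The direct effect of attrition is small.** This stands. On the basis that nearly reproduces 430, the stated 80% survives a 10% loss and is missed by about one point at 20%. A reader might infer that the missing allowance by itself makes the power materially wrong, or that dropout explains a fall to about 69%. The figures support neither reading, because most of that fall is present with no loss at all. Holding the design effect at 3.82 would show a steeper fall (72.4% one-sided at 20% loss), but that is wrong when the centres remain and only patients leave.
- **The nominal design has some margin.** At 48 per centre there are 1680 per arm, and one-sided power is 80.3% at 10% loss and 79.2% at 20%. This is true, but the margin is about 2% and is not intended for attrition.
- **Imputation does recover information.** The diagnostic interview is repeated at 6 and 12 months, so a patient who becomes a case early and then leaves is already a known event. Risk variables are also re-measured at each visit. This stands, and it rules out saying that imputation does nothing for power. But it recovers only part of the loss. The 1% limit on power loss in the Multiple imputations section governs the number of imputations, not the outcomes that are missing.
- **The model adjusts for a strong predictor.** The baseline risk score has a reported C-index of 0.82, so adjustment could offset a few points. The document does not allow this to be sized, and the plan's own calculation takes no credit for it.
- **A journal article condenses the full protocol, which may give a loss rate.** That is possible. But this section sets out its inputs in full and names the one inflation it applies, and the abstract enrols the uninflated number.

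**Conclusion.** The point holds in two parts of unequal weight.

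First, recruitment equals the number that the formula needs analysed, and 18-month loss is not allowed for. For assumed losses of 10–30% spread evenly over 35 centres per arm, this costs about 1 to 4 points of power, because at an intraclass correlation of 0.06 the number of centres dominates. Loss of whole centres or uneven loss would cost more.

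Second, and larger, 430 fits only a one-sided 5% test and the sidedness is not stated. If the test is two-sided, power is about 71% with no loss and about 67–70% with 10–30% loss. If it is one-sided, the 80% is close to right. The document does not say which applies, so the size of the overstatement depends on that answer.

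The figures come from an unadjusted comparison of 12% with 7% and count only patients with observed outcomes. On that basis, power after imputation should lie between the no-loss row and the relevant loss row.

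**What to change.** In the Sample size section, state whether the 5% test is one- or two-sided and what 18-month loss is assumed. Restate the power at the number analysed, with the two effects apart. For example, with 35 centres per arm, 1643 enrolled per arm and an intraclass correlation of 0.06, power is 81% one-sided or 71% two-sided with no loss, and 79% or 69% if 20% are lost. The 20% should be replaced by the team's own expectation.

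In Strengths and limitations, qualify the remark on imputation rather than delete it: it uses the interim interviews and repeated covariates to recover part of the information lost, and does not restore the planned power in full.

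No extra patients are needed for this, and adding them within the same centres would be an inefficient answer to the sidedness gap. With 35 centres per arm, effective n cannot exceed 35/0.06 = 583, and reaching 539 would take 539 × 0.94/(1 − 539 × 0.06/35) ≈ 6,667 patients per arm, about 190 per centre. The cost is wording, and a less favourable stated power.

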### Follow-up

All patients enrolled in the trial will be evaluated at baseline, 6, 12 and 18 months. Interviewers trained and independent from the FPs providing usual care or the new intervention will administer the CIDI and the other questionnaires. FPs participating in the trial will complete a self-administered questionnaire at baseline.

### Variables

#### Main outcome

Our primary outcome will be the cumulative incidence of major depression during 18 months of follow-up. We will use the section of depression of the CIDI [54,55], developed and validated by the WHO [56]. The CIDI is a fully structured diagnostic interview that provides current diagnoses according to DSM-IV categories. We will use it to estimate the onset of major depression in each prior 6-month period (0–6, 6–12, and 12–18 months). Interviewing in this way, at baseline, 6, 12 and 18 months, we will obtain the most accurate picture of the cumulative incidence of major depression.

#### Secondary outcomes

As secondary outcomes we will use measurements of health-related quality of life using the 12-item Short Form (SF-12) [57,58] and the EuroQol [59-61] with evaluations at baseline, 6, 12 and 18 months. Furthermore, we will make estimates of cost-effectiveness and cost-utility (see Economic evaluation below).

#### Independent variables

##### Patient variables

• Socio-demographic characteristics: province, sex, age, marital status (married/living with partner, separated, widowed, divorced or single), employment status (employed, unemployed/looking for a job, retired, unable to work, looking after family or home, in full-time education, and other), educational level (beyond secondary education, secondary education, primary education and incomplete primary education/illiterate), owner-occupier of an accommodation (owner, mortgage, rented, and other), living alone or with others [62].

• Anxiety disorders using the anxiety section of the Primary Care Evaluation of Mental Disorders (PRIME-MD) [63]. The Spanish version of the PRIME-MD can classify patients who test positive for panic attack, generalized anxiety disorder and other anxiety disorders [64]. We will use a dichotomous anxiety variable to indicate when any of the three diagnoses of anxiety are present in a given patient.

• Controls, demands and rewards for unpaid work, using an adapted 7 item version of the job content instrument [65]. From the sum of the seven items, the variable is categorized in 3 (satisfied, dissatisfied and very dissatisfied).This questionnaire has previously shown good validity and reliability in Spain [62].

• Satisfied with living together at home (5-Likert response options).

• A lifetime screen for depression based on the first two questions of the CIDI [66].

• Childhood experiences of physical abuse (5-Likert response options) [67].

• Presence of serious physical, psychological or substance misuse problems, or any serious disability, in persons who are close friends or relations of participants. These questions can be used as 4 different items (yes/no) or as an ordinal variable (summation of the 4 questions).

• Whether the participant’s mother committed suicide (yes/no) [68].

• Perception of safety inside and outside the home using a question from the Health Surveys for England with 5-Likert response options [69].

• Experiences of discrimination on the grounds of sex, age, ethnicity, appearance, disability, sexual orientation, and others using 7 questions (yes/no) from a European study [70]. The answers to these seven items can also be joined in an ordinal variable.

• Taking medication for anxiety, depression or stress in the previous 6 months (yes/no).

• Probability of the onset of major depression at 12 months, obtained from the equation “predictD-Spain”, which has been previously validated [34] and is derived from a combination of some of the above variables.

We will assess all these variables and questionnaires at baseline, 6, 12 and 18 months. The test–retest reliability of questions used in the predictD studies has been reported previously [62,71].

##### Family physician variables

The FP variables will be collected through a self-administered questionnaire at baseline:

• Age and gender.

• **Job characteristics**: urban or rural clinic, type of contract (fixed or temporary/substitute), months working at the current Health Center, list size and mean time per visit.

• **Training**: year medical degree, time working as FP (in months), postgraduate training (3 or 4 years) in family medicine (yes/no), accreditation as a FP tutor (yes/no), experience in training FPs [resident 1^st^ year assigned (yes/no), and/or resident 3^rd^ or 4^th^ year assigned (yes/no)], and membership of Spanish Health & Communication group (yes/no).

• **Satisfaction with management of patients with mental health disorders in primary care**: degree of comfort in the use of antidepressants (5-Likert response options), satisfaction with communication and care shared with the mental health team (secondary care) (5-Likert response options), satisfaction with the role of primary care nurse in mental health disorders (5-Likert response options) and satisfaction with the role of primary care social worker in mental health disorders (5-Likert response options or “I do not have social worker in my health center”).

• **Profile of professional practice**: A three-dimensional questionnaire about professional satisfaction (4 items), workload perception (4 items), and biomedical vs. psychosocial orientation (4 items) validated in Spain [72].

• **Personality** according to the Spanish version of the Eysenck Personality Questionnaire-Revised (EPQR-A) [73-75], which explores three dimensions: extraversion, neuroticism, and psychoticism.

##### Health center variables

From administrative records we will collect at baseline the following variables: inhabitants of the health center area (Basic Zone Area), size of the population where the health center is located, number of professionals (also by type of professionals) in the health center, population/professional ratios, and time of functioning as health center.

### Statistical analysis

In line with recommendations by Groenwold [76], we will perform effectiveness analyses in the following ways: analysis with covariate adjustment and 2) intention-to-treat analysis by multiple imputations with covariate adjustment. We will conduct all analyses using Stata, release 12.1 [77].

#### Multiple imputations

We will use multiple imputations by chained equations [78] by means of the ‘ICE’ program [79]. We will choose a number of imputations to limit the loss in power (no more than 1%) for testing the association of interest [80]. We will undertake a sensitivity analysis to check the changes in the estimates and variances with progressive increases in the number of imputations [78]. We will explore the plausibility of the missing at random assumption and will include in the imputation models any covariate of interest that is predictive of missingness [81]. When we have to impute a covariate, we will also include the outcome variable in the imputation model. Standard errors will be calculated using Rubin’s rules [82] which take account of the variability in results between the imputed datasets, reflecting the uncertainty associated with the missing values.

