#### Cost effectiveness and cost-utility analysis

As in the effectiveness analyses, we will take two approaches to the cost-effectiveness and cost-utility analyses: 1) a complete case analysis with covariate adjustment and 2) an analysis after multiple imputations with covariate adjustment. For the first strategy we will apply the inverse probability weighting to the final model. We will calculate incremental cost-effectiveness ratios (ICER), which are calculated as incremental cost (mean cost for intervention group minus mean cost for control group) divided by incremental effectiveness (mean effect for intervention group minus mean effect for control group) [93]. Incremental cost-utility ratios (ICUR) will be calculated in the same way. The only difference is that the effect will be the difference in QALYs. The incremental costs and incremental health effects will be modeled by generalized linear models (GLM). The modified Parks test will be used in order to select the appropriate family. In order to identify the correct link function we will compare model performance of all permutations of candidate link and variance function using different diagnostic tests such as the Pregibon Link test, the Hosmer-Lemoshow test and the Copas test [93]. We will check the intraclass correlation coefficients and the likelihood-ratio tests with health center, FP and both as we said before. If the clustering effect is relevant, we will use robust standard errors for the cluster indicated.

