#### Quantification of uncertainty

To estimate the uncertainty around the ICER and ICUR, we will calculate 95% confidence intervals around the mean cost differences using the non-parametric confidence interval. Bootstrapping with 5000 replications will be performed on each imputed dataset [93,94].

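### The economic analysis makes clustering optional although health centers are randomised, and the robust standard errors it names do not carry into the bootstrap; the imputation also names no center term

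*Protocol article*

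**What the plan says.** In the protocol article, Randomized allocation assigns health centers, not patients: 35 per arm, five per arm in each of seven cities. Sample size pays for this "with the assumption that the intraclass correlation coefficient of the health center is 0.06", giving a design effect of 3.82.

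The analysis sections treat that clustering unevenly:

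- **Regression models** (effectiveness): multilevel logistic regression, with health center and then family physician tested as random factors.
- **Cost effectiveness and cost-utility analysis**: generalized linear models for costs and effects. Intraclass correlations and likelihood-ratio tests are inspected first, and then: "If the clustering effect is relevant, we will use robust standard errors for the cluster indicated".
- **Quantification of uncertainty**: confidence intervals from a non-parametric procedure. "Bootstrapping with 5000 replications will be performed on each imputed dataset". The unit drawn is not named. The section that follows builds the cost-effectiveness planes and acceptability curves from these draws.
- **Multiple imputations**: "We will use multiple imputations by chained equations [78] by means of the ‘ICE’ program [79". The section asks for covariates that predict missingness, and for the outcome when a covariate is imputed. It names no health-center or physician term.

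**The concern.** Because centers are randomised, clustering is a property of the design. Whether it counts should not depend on a test in the same data. A test can miss a modest correlation, and the standard errors are then too small. The wording also lets the check point to the physician level, which lies below the unit of randomisation.

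The second difficulty is that the remedy sits in a different place from the reported uncertainty. A cluster-robust standard error changes the standard error of a regression coefficient. It does not change the point estimate computed in each bootstrap replicate, and the spread of those estimates is what yields the intervals, planes and acceptability curves. If the replicates draw individual patients, the economic results ignore the design even when the check has found clustering. The probability of being cost-effective would then look more certain than it is.

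The imputation raises a smaller version of the same question. Outcomes imputed without regard to center carry no center effect, so the completed data show less between-center variance than the real data.

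**Working it through.** **Inputs from the article (Sample size):** 48 patients per center, 35 centers per arm, intraclass correlation ρ = 0.06 for depression, control incidence 12%, and 430 per arm before inflation. **Not given, so assumed:** ρ for costs and QALYs (0.01 to 0.06) and the share m of patients with a missing outcome (5% to 25%).

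**1. The plan's own figure.** Design effect DE = 1 + (48 − 1) × 0.06 = 3.82. Then 430 × 3.82 = 1642.6, which rounds up to the stated 1643 per arm. Both reproduce. The 430 is taken as given here.

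**2. Can the relevance check miss real clustering?** As an approximation, take a 5% F test on 70 centers of 48 with a normal outcome. It misses with probability P[F(69, 3290) < F₀.₉₅ / (1 + 48ρ/(1 − ρ))]. At ρ = 0.01 this is about 24%; at ρ = 0.02, about 1%. The condition therefore does harm mainly when the correlation is small.

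**3. Bootstrap of individual patients.** The interval has 1/√DE of the correct width, and coverage is 2Φ(1.96/√DE) − 1, with DE = 1 + 47ρ.

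| ρ | DE | Width relative to correct | Coverage of nominal 95% |
|---|---|---|---|
| 0.01 | 1.47 | 0.82 | 89% |
| 0.02 | 1.94 | 0.72 | 84% |
| 0.03 | 2.41 | 0.64 | 79% |
| 0.06 | 3.82 | 0.51 | 68% |

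A simulation of the binary outcome at ρ = 0.06 (600 trials, beta-binomial centers) gave 66% coverage when patients were resampled and 93% when centers were.

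**4. Imputation without center, then a cluster-aware analysis.** Variances are relative to σ²/n for one arm of planned size n.

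- Variance from Rubin's rules: T = 1/(1 − m) + 47ρ(1 − m)². Only pairs of patients who are both observed keep their correlation.
- True variance: V = [1 + (48(1 − m) − 1)ρ]/(1 − m).
- Type I error: 2[1 − Φ(1.96√(T/V))].

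At ρ = 0.06, when missing patients carry no outcome information:

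| m | T | V | √(T/V) | Type I error |
|---|---|---|---|---|
| 5% | 3.598 | 3.869 | 0.964 | 5.9% |
| 15% | 3.214 | 3.986 | 0.898 | 7.8% |
| 25% | 2.920 | 4.133 | 0.840 | 10.0% |

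Simulation at 25% missing gave 10.4% to 10.6%. At ρ = 0.01 and m = 25%, T = 1.598, V = 1.800 and type I error is 6.5%.

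**5. Keeping onsets already seen.** The CIDI is also given at 6 and 12 months, so some patients who drop out have a known outcome. Suppose the 25% lost are equally likely to miss first at 6, 12 or 18 months, and onsets are spread evenly over the three periods. Then (0 + 1/3 + 2/3)/3 = 1/3 of their onsets are known, and the effective missing share is 0.25 × 2/3 = 0.167. This gives T = 3.158, V = 4.008, ratio 0.888 and type I error 8.2%. A simulation with the same loss spread over the visits gave a ratio of 0.92 and about 7%. The range is therefore about 7% to 8%.

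**The case against.** The strongest reply is that a condensed article need not list every imputation covariate or name the resampling unit. This has force:

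- The Multiple imputations section gives two requirements, not a closed list. It does not bar a center term, and chained equations can carry center indicators or center-level covariates.
- A bootstrap that draws whole centers is also non-parametric, and nothing in the text says that patients are drawn.
- Imputed data still go into a multilevel model, and a weighted complete-case analysis stands beside it. A cluster-aware complete-case analysis held about 95% coverage in simulation, so a marked discrepancy between the two would be visible.
- The value 0.06 belongs to depression. It applies at most to the incidence difference, not to costs or QALYs.
- The economic results are secondary.

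A reader might infer that clustering is lost from the intention-to-treat analysis, and that its intervals and the economic ones will certainly be too narrow. The documents do not support that. For the primary outcome the between-center variance would at most be diluted, and only if center is omitted. For the bootstrap, the undercoverage follows only if patients are the resampling unit.

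The reply does not reach the conditional clause. It is stated, not inferred, and it is the wrong rule for a center-randomised trial. Nor does it answer the gap between robust regression standard errors and the bootstrap that supplies the reported uncertainty.

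**Conclusion.** The point holds for the economic analysis. Allowance for clustering is conditional when it should be automatic, and the one device named does not carry into the bootstrap. If patients are resampled, nominal 95% intervals cover about 89%, 84% and 68% at intraclass correlations of 0.01, 0.02 and 0.06. These figures assume equal centers of 48 and approximate normality, over a range of correlations that the article does not give for costs or QALYs.

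The imputation is a secondary point and depends on center being left out. At 0.06, type I error would be about 6% with 5% missing and up to about 10% with 25% missing and no outcome information, or about 7% to 8% if earlier onsets are kept. The article gives no dropout figure, and at lower correlations the effect is smaller. This is a reason to specify the imputation model, not evidence that the primary analysis is invalid. The planned sample size is unaffected.

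**What to change.** 1. **Economic models:** delete the condition that clustering be judged relevant. Account for health center in every cost and effect model.
2. **Bootstrap:** state that whole health centers are resampled within arm and city in each imputed dataset, with each patient's cost and effect kept together. There are only five centers per arm in each city, so drawing five from five understates the between-center variance by a factor of 4/5 (standard error × √0.8 = 0.89). Drawing four from five, or rescaling, corrects this.
3. **Imputation:** include health center (for example, a two-level imputation model with a random center intercept) and the 6- and 12-month CIDI results, so that onsets already recorded are kept.

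The cost is wording in the analysis plan and some programming. It needs no new data and no extra patients. The intervals will be wider and the acceptability curves flatter than under patient-level resampling.
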